## IX -1- 6- Secondary analyses

A linear mixed effects regression model will be used to compare the variations between the groups of the quantitative secondary endpoints (number of days of sick leave, number of periods of sick leave, pain, Quebec scale, MOS SF-12, HAD, FABQ and CSQ). The variable to be studied will therefore be the difference between the randomisation value (D0) and that of interest (1 year), as well as the difference between the randomisation visit and those of the interim visits (3 months and 6 months). The difference in the Δ between the groups will be modelled with the following fixed effects: the group variable (2 modalities), the enrolment value as a quantitative covariate (centred variable), the visit variable (3 modalities) and the interaction between the time and the visit, allowing us to estimate the treatment effect at each visit. The model will therefore allow us to compare the adjusted means (to the baseline value and the values of the interim visits) of the variations between the final visit and the enrolment visit (as well as between the interim visits and the enrolment visit). A random effect on the patient will be added to this model in order to take into account the correlation induced by the repetition of the measurements performed in the same patient. This linear mixed model for repeated measurements (MMRM) allows the assessments performed at each visit to be taken into account, as well as the randomly missing data (the model will also integrate the endpoint values at the different visits, enrolment variables which are potentially predictive of the missing data). The area under the curve of pain between enrolment and 1 year, assessed every week, will be calculated using the trapezoidal rule and compared using the non-parametric Mann–Whitney U test. The Q-TWIST will be calculated from the percentage of time spent by a patient in various states (percentage of time spent in inactivity, time spent with acceptable pain (less than 3 on a scale from 0 to 10 which corresponds to the PASS), time spent with pain greater than 3). The values assigned to these states will be defined at the time of the blind review of the data. The means will be compared using the non-parametric Mann–Whitney U test.

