## I - 3 - EXPECTED RESULTS AND PROSPECTS

The study will be conducted in patients between the ages of 18 and 60 who have been on sick leave due to lower back pain for between 4 and 24 weeks.

Two groups will be studied in parallel: one will undertake a short (5-day) spa therapy intervention, during which they will receive a programme consisting of physical exercises, spa baths, psycho-behavioural treatment and therapeutic education. The other group (the control group) will receive standard care and advice typically given in these situations by general practitioners and specialists. Both groups will receive a guide on lower back pain.

While the efficacy of this programme has been demonstrated, it must be shown to lead to an increase in the return-to-work rates, improvement in pain and functional incapacity, and a quicker recovery. This would be the first treatment programme to demonstrate efficacy in this situation in France.

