## II - 2 - SECONDARY OBJECTIVES

To evaluate the efficacy of a short, intensive and standardised spa therapy intervention on the number of days of sick leave between 6 months and 1 year, as well as pain, function and quality of life at 1 year for patients on sick leave due to lower back pain from 4 to 24 weeks’ duration and for those in which an extended period of sick leave is expected.

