## IV - 3 - REQUIRED NUMBER OF SUBJECTS

The return-to-work rate at 1 year is estimated to be 70% in the control group. The hypothesis is to reach 80% in the intervention group. With a 5% risk and a power of 80%, a total of 600 patients are planned to be enrolled: 300 patients in the short spa therapy group and 300 patients in the control group. Taking into account the risk of loss-to-follow-up, 700 patients will be enrolled.

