## VI - 2 - SECONDARY ENDPOINTS

The secondary endpoints will be as follows:

- Area under the curve of pain over the past 48 hours, assessed every fortnight using a numeric scale from 0 to 100 at 1 year;
- Functional assessment at 1 year (Quebec scale);
- Quality of Life assessment at 1 year (MOS SF-12 questionnaire);
- TWIST at 1 year (pain);
- Number of days of sick leave between 6 months and 1 year after enrolment. We have not taken into account the total number of days of sick leave as, by definition, the intervention requires the patients to be available for the duration of the treatment, which will involve sick leave.

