## IX -1- 5- Primary endpoint analysis

An intention-to-treat analysis will be carried out, i.e., all patients randomised will be analysed in their randomisation arm, regardless of the treatment received and any missing information. The bilateral tests will be carried out at the 5% threshold. The return-to-work rate percentage will be compared using the Chi-squared test.

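### The protocol defines two different secondary endpoint sets: five endpoints at 1 year or over months 6 to 12 in VI-2, but eight mixed-model variables compared at up to three visits in IX-1-6

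*Protocol*

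**What the plan says.** **VI-2 and the Summary** give a closed list of five secondary endpoints: AUC of pain over 1 year, Quebec scale at 1 year, SF-12 at 1 year, TWIST at 1 year, and days of sick leave between 6 months and 1 year. The time is part of the definition, for example "Functional assessment at 1 year (Quebec scale"). VI-2 also explains why total sick-leave days are not used: attending the intervention itself entails sick leave. The secondary objective in II-2 matches this list, naming sick-leave days in the second half-year "as well as pain, function and quality of life at 1 year".

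**The Summary's statistical paragraph** sends AUC and TWIST to the Mann–Whitney test and the other quantitative secondary endpoints to a mixed model. On the VI-2 list, that leaves three variables for the model: Quebec, SF-12 and sick-leave days.

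**IX-1-6** names eight for the same model: "quantitative secondary endpoints (number of days of sick leave, number of periods of sick leave, pain, Quebec scale, MOS SF-12, HAD, FABQ and CSQ"). The response is the change from D0 to 1 year and also to 3 and 6 months, with an interaction described as "allowing us to estimate the treatment effect at each visit". Mann–Whitney tests of AUC and Q-TWIST follow.

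**Significance level.** The only statement is in IX-1-5, under the primary analysis: "The bilateral tests will be carried out at the 5% threshold". IX-1-6 gives none.

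**The concern.** A protocol should fix which endpoints are secondary and at what time. Here two sections answer differently under the same name. A SAP written from VI-2 and one written from IX-1-6 would contain different secondary analyses, and either could cite the protocol.

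Three things follow.

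- Number of sick-leave periods, HAD, FABQ and CSQ gain secondary status only in the analysis section.
- Sick-leave days are compared in the early interval that VI-2 excludes for a stated reason. Only the spa arm attends the course, so the early comparison carries a component created by the intervention itself.
- A change from D0 is specified for sick-leave periods, although the schedule of assessments collects no D0 value.

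The wider set also offers more chances for a nominally significant result to be reported as a secondary endpoint. Most of these measures are patient-reported, and III-4 itself calls pain, function and quality of life subjective.

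**Working it through.** **1. The plan's own figure.** IV-3 gives the control rate: "The return-to-work rate at 1 year is estimated to be 70% in the control group". For the spa arm it then sets the target: "The hypothesis is to reach 80% in the intervention group". With two-sided 5%, 80% power and pooled variance, n per arm = [1.96·√(2·0.75·0.25) + 0.8416·√(0.7·0.3 + 0.8·0.2)]² / 0.10² = (1.2002 + 0.5119)² / 0.01 = 293.2, so 294 per arm and 588 in all. The stated 600 is reproduced within rounding, and 300 per arm gives power 0.809. The planned size and its 5% level concern one primary comparison. Nothing below alters it.

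**2. The two sets side by side.**

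| Variable | VI-2 | IX-1-6 | Comparisons under IX-1-6 |
|---|---|---|---|
| Pain AUC | yes, over 1 year | Mann–Whitney | 1 |
| TWIST | yes, at 1 year | Mann–Whitney | 1 |
| Quebec | yes, at 1 year | M3, M6, M12 | 3 |
| SF-12 | yes, at 1 year | M3, M6, M12 | 3 |
| Sick-leave days | yes, months 6–12 only | M3, M6, M12 | 3 |
| Pain at visits | no (AUC only) | M3, M6, M12 | 3 |
| HAD | no | M3, M6, M12 | 3 |
| Sick-leave periods | no | M3, M6, M12 | 3 |
| FABQ | no | M12 (only follow-up measurement, VII-3) | 1 |
| CSQ | no | M12 (only follow-up measurement, VII-3) | 1 |

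Total under IX-1-6: 6 × 3 + 2 + 2 = 22, counting one score per instrument. The schedule marks sick-leave periods at M3, M6 and M12 but not at D0. If the change cannot be computed, three comparisons drop out, leaving 19. Separate subscales of SF-12, HAD, FABQ or CSQ would raise the count.

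**3. Sick-leave days.** VII-3 collects sick leave since the previous contact. The M12 value therefore covers the interval after Month 6 and fits VI-2. The M3 and M6 values cover the interval before it, which VI-2 leaves out. VII-1 allows up to 3 months between enrolment and therapy, so the course itself falls in that excluded interval.

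**4. What the difference does to the error rate.** Assumptions: no effect on any secondary variable; every comparison tested at two-sided 5%; a common correlation ρ between test statistics. The documents give no correlations, so a range is shown.

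- Independent tests: 1 − 0.95^k. For k = 5 this is 22.6%; k = 19, 62.3%; k = 22, 67.6%. In favour of the spa only, 1 − 0.975^k gives 11.9%, 38.2% and 42.7%.
- Correlated tests: Z_j = √ρ·A + √(1−ρ)·E_j, with A and E_j independent standard normal. The chance is that any |Z_j| exceeds 1.96 (either direction) or any Z_j exceeds 1.96 (favouring the spa).

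| ρ | 5 tests: either / spa | 19 tests: either / spa | 22 tests: either / spa |
|---|---|---|---|
| 0.2 | 22% / 11% | 57% / 31% | 62% / 34% |
| 0.5 | 18% / 9% | 41% / 20% | 44% / 22% |
| 0.8 | 13% / 6% | 22% / 11% | 23% / 11% |

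A more realistic structure (correlation 0.2 to 0.7 between outcomes and 0.5 to 0.7 between visits of one outcome, with AUC and TWIST tied to pain) gives 59% to 36% for 22 tests in either direction and 33% to 18% in favour of the spa. This lies inside the range above.

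**The case against.** The strongest reply is that there is nothing to control. The trial has one primary endpoint at one time and one powered comparison, and VI-1 ties the case for the intervention to return to work. IX-1 announces a SAP, to be validated before database freeze, and multiplicity among secondary endpoints is commonly settled there. IX-1-6 calls Months 3 and 6 interim visits and treats 1 year as the time of interest. The extra scales are openly scheduled. All of this stands. The absence of a testing order, a Holm rule or a gate on the primary is therefore not a defect of this protocol.

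A reader might also infer that a false efficacy claim is likely. The figures do not support that. A false result favouring the spa is about 11% to 34% at the assumed correlations and 43% even if all 22 tests were independent. Nor does IX-1-6 say that each comparison is tested at 5%; that is inferred from a sentence under the primary analysis, plural in wording and the only level given.

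Finally, a reader might take I-3 as licensing separate claims, since it says of the programme that "it must be shown to lead to an increase in the return-to-work rates, improvement in pain and functional incapacity, and a quicker recovery". But I-3 states prospects and sets no decision rule, and it joins its outcomes with *and*. Read as a criterion, it would require all of them, which makes a false claim harder, not easier.

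What the reply does not answer is the mismatch. Which endpoints are secondary, and at what time, is protocol content. A SAP cannot follow both lists.

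**Conclusion.** The point holds as an internal contradiction about the secondary endpoint set. VI-2 and the Summary fix five endpoints at 1 year or over months 6 to 12. IX-1-6 adds four variables and visit-level pain, extends the comparisons to Months 3 and 6, uses sick-leave days in an interval VI-2 excludes, and specifies a change from D0 for a variable with no scheduled D0 value.

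The effect is about 19 to 22 comparisons in place of 5. If all are tested at two-sided 5% under no effect, the chance of some false positive rises from about 13–22% to about 23–62% for 22 tests (slightly lower for 19). These figures rest on assumed correlations of 0.8 to 0.2 and one score per instrument. They show the cost of the wider reading and are not an error rate of the primary analysis, which is unaffected. The matter should be put right before the SAP is final.

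**What to change.** Add to IX-1-6, in substance:

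1. The secondary endpoints are the five of VI-2, at the times stated there. Sick-leave days are analysed only over months 6 to 12.
2. Number of sick-leave periods, visit-level pain, HAD, FABQ, CSQ and all Month 3 and Month 6 comparisons are exploratory. They are reported as estimates with 95% confidence intervals and without efficacy claims.

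For sick-leave periods, describe the follow-up counts directly unless a D0 value is in fact collected. An order or a Holm adjustment among the five is optional and can be left to the SAP.

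The cost is wording in the protocol, carried into the SAP before database freeze. Patients, data collection, the mixed model and the primary test stay as they are. The small price is that results on the additional scales and at the interim visits become supportive only.

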**Local recruitment (local press**

**posters in pharmacies, doctors’ waiting**

**rooms) and at medical visits**

Assessment at D0

Intervention (spa therapy, group therapeutic education and back guide)

Follow-up at 3 months, 6 months and 1 year by post or email

+ numeric pain scale every fortnight by telephone

|  | **Enrolment visit + randomisation** | **Intervention**  **Visit** | **Visit 1**  **Mail/**  **phone** | **Visit 2**  **Mail/**  **phone** | **Visit 3**  **Mail/**  **phone** |
| --- | --- | --- | --- | --- | --- |
|  | D0 | M1-M3  Maximum after intervention | M3 | M6 | M12 |
| Inclusion and exclusion criteria | + |  |  |  |  |
| **Information and consent for the cohort study** | + |  |  |  |  |
| **Randomisation** | + |  |  |  |  |
| **Information and consent to participate in the therapy for patients randomised into the experimental arm** | + |  |  |  |  |
| **Patient contact information** | + |  |  |  |  |
| **Medical examination** | + |  |  |  |  |
| **Back guide and patient diary issued** | + |  |  |  |  |
| ASSESSMENT: | | | | | |
| - Socioprofessional information | + |  |  |  |  |
| - Clinical information regarding lower back pain | + |  | + | + | + |
| - Number of days of sick leave | + |  | + | + | + |
| - Return to work |  |  | + | + | + |
| - Number of periods of sick leave |  |  | + | + | + |
| - Treatments | + |  | + | + | + |
| - Numeric pain scale | + |  | + | + | + |
| - Quebec | + |  | + | + | + |
| - HAD | + |  | + | + | + |
| - MOS SF-12 | + |  | + | + | + |
| - FABQ | + |  |  |  | + |
| - CSQ | + |  |  |  | + |
| - Treatment satisfaction scale |  |  |  |  | + |
| **Adverse Events** |  | + | + | + | + |
| **INTERVENTION: Intensive spa therapy** |  | + |  |  |  |

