# IV – STUDY POPULATION

## IV - 1 - INCLUSION CRITERIA

- Men or women aged from 18 to 60 years (inclusive);
- Isolated lower back pain or back and radicular pain after classification of the disease (with the lower back numeric pain scale score being higher than the radicular numeric pain scale score);
- Patients on sick leave due to common lower back pain from 4 to 24 weeks’ duration and those in which an extended period of sick leave is expected;
- Medical examination carried out in advance, the results of which will be communicated to the patient;
- Patients having provided their written informed consent to take part in the study;
- Patients affiliated with a social security scheme (beneficiary or entitled).

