  - Coping strategies: CSQ questionnaire.

Following this visit, the investigator will give the Month 3, 6 and 12 follow-up self-assessment questionnaires which the patient must fill in and return by mail, from the enrolment visit for the control group and from the end of spa therapy for the intervention group.

Patients randomised into the standardised spa therapy arm will receive a start date for the intervention from the secretary at the spa therapy centre, taking into account a maximum time period of 3 months between the enrolment visit and the therapy. The planning of the stay and patient welcome will be arranged by the spa therapy centre, the choice of accommodation will be managed by the French Association for Spa Therapy Research (AFRETH) and transport passes will be managed by the Clinical Research Unit (URC).

Finally, the investigator will provide the patients with the guide on lower back pain, the patient diary containing the self-assessment questionnaires for the various evaluations, as well as the patient card mentioning the patient’s participation in the study.

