## VII - 3 - FOLLOW-UP VISITS after the intervention

Patients will undergo follow-up at Months 3, 6 and 12. Follow-up will be done by post or email, depending on the patient’s preference, together with a telephone call if no response is received.

The following data will be evaluated:

- Professional status and return to work;
- Periods of sick leave since the previous visit (dates and number of days of sick leave);
- Assessment of pain over the past 48 hours, assessed using a numeric scale from 0 to 100;
- Lower back pain progress;
- Treatment since the previous visit;
- Adverse events collected;
- Functional indices: Quebec scale;
- Anxiety/Depression: HAD questionnaire;
- Quality of Life: MOS SF-12 questionnaire;
- Fear-avoidance beliefs: FABQ questionnaire (only at the Month 12 assessment);
- Coping strategies: CSQ questionnaire (only at the Month 12 assessment);
- Treatment satisfaction (only at the Month 12 assessment).

Pain over the past 48 hours will also be systematically evaluated once every fortnight by phone (using a numeric scale from 0 to 100). VOICE RESPONSE SYSTEM

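### The number of sick-leave periods is tested between arms although a low count can mean either sustained work or unbroken leave, so the result cannot be read as benefit or harm

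*Protocol*

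**What the plan says.** Section IX-1-6 of the protocol puts the "quantitative secondary endpoints (number of days of sick leave, number of periods of sick leave, pain, Quebec scale, MOS SF-12, HAD, FABQ and CSQ" into one linear mixed model, with a treatment effect at each visit. For all of them, "The variable to be studied will therefore be the difference between the randomisation value (D0) and that of interest (1 year", with the 3- and 6-month visits handled likewise.

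Section VII-3 collects the data at Months 3, 6 and 12 as "Periods of sick leave since the previous visit (dates and number of days of sick leave". The counting window is therefore a calendar interval: roughly months 0-3, 3-6 and 6-12.

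Section IV-1 admits "Patients on sick leave due to common lower back pain from 4 to 24 weeks" in duration, so everyone is on leave at enrolment. Section IV-3 states the trial's hypothesis: "The return-to-work rate at 1 year is estimated to be 70% in the control group. The hypothesis is to reach 80% in the intervention group".

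The endpoint list in VI-2 contains the number of days of leave between 6 months and 1 year, but not the number of periods. Apart from a line in the schedule of assessments ("Number of periods of sick leave", marked at M3, M6 and M12 only), the count becomes a tested endpoint solely through IX-1-6.

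**The concern.** A patient who is still on the leave that brought them into the trial cannot start another one. The opportunity to add to the count arises only after the initial leave ends, and how soon and how often it ends is what the spa therapy is meant to change. Section IX-1-6 neither takes account of time off the initial leave nor says how a leave that is still running is scored.

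Two hypothetical M6-M12 records show the difficulty. A patient off work throughout has about 182 days of leave and scores 0 periods (new periods only) or 1 (ongoing leave counted). A patient back at work with two 3-day relapses has 6 days of leave and scores 2. On either rule the count ranks the first patient as the better outcome, contrary to the primary objective. At stake is a tested secondary result that may contradict, or fail to reflect, a real gain in return to work and days of leave.

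**Working it through.** **Inputs from the protocol.** Return to work at 1 year 70% (control) and 80% (spa); 300 evaluable patients per arm; two-sided 5% tests (IV-3, IX-1-5). As a check on these inputs, the pooled-variance formula gives n = [1.96·√(2·0.75·0.25) + 0.8416·√(0.70·0.30 + 0.80·0.20)]² / 0.10² = (1.200 + 0.512)² / 0.01 ≈ 293.2, so 294 per arm or 588 in total. This agrees with the planned 600.

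**Assumptions.** The protocol gives no relapse rate and no length of relapse. The 70% and 80% are read as the shares whose initial leave has ended by month 12. Relapse per returner is set equal in the two arms, so that any difference in the count comes only from time off the initial leave.

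**Closed form near month 12.** Let L be the mean number of new periods per returner in the window.

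- New periods only: control 0.70·L, spa 0.80·L. The ratio is 0.80/0.70 = 1.14 for any L. The spa arm would need to cut relapse per returner by 1 − 0.70/0.80 = 12.5% just to tie.
- Ongoing leave counted as one period: control 0.30 + 0.70·L, spa 0.20 + 0.80·L. The difference (spa − control) is 0.10·(L − 1).

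| L | Control | Spa |
|---|---|---|
| 0.5 | 0.65 | 0.60 |
| 1.0 | 1.00 | 1.00 |
| 1.2 | 1.14 | 1.16 |

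Under the second rule the sign changes at L = 1.

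**Simulation of the M6-M12 window.** Further assumptions: exponential time to the end of the initial leave, calibrated to 70% and 80% by 1 year; relapses lasting 14 days on average; relapse rate varied from 0.25 to 2 per half-year at work. The spa/control ratio of new periods is about 1.17 to 1.18 (up to 1.19 between runs), while the ratio per day at work is 0.99 to 1.01. Mean days of leave, control v spa, are 76.8 v 58.5 at the lowest rate and 89.3 v 72.5 at the highest. With 300 per arm, the expected difference divided by its standard error (unadjusted; repeat runs move it by up to 0.1) is:

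| Relapse rate per half-year at work | Mean count with ongoing leave, control v spa | Difference/SE, ongoing leave counted | Difference/SE, new periods only |
|---|---|---|---|
| 0.25 | 0.70 v 0.63 | −1.59 | 0.76 |
| 0.5 | 0.85 v 0.80 | −0.96 | 1.02 |
| 1 | 1.13 v 1.13 | 0.03 | 1.41 |
| 2 | 1.63 v 1.73 | 1.15 | 1.92 |

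Negative values favour the spa arm. For days of leave the same quantity is near −2.9 throughout.

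**Reading these as chances of significance.** For new periods only, the chance of a significant result against the spa arm is Φ(0.76 − 1.96) = Φ(−1.20) ≈ 0.12 at the lowest rate and Φ(1.92 − 1.96) = Φ(−0.04) ≈ 0.48 at the highest. For days of leave, the chance of a significant result in favour of the spa arm is Φ(2.9 − 1.96) = Φ(0.94) ≈ 0.83.

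**The case against.** Three points on the other side carry weight.

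First, comparing counts per randomised patient over a fixed window is a legitimate intention-to-treat contrast. It estimates the total effect on the number of absences and is not biased for that quantity. The rate per day at work is a different quantity, and it conditions on something that happens after randomisation. This stands: the defect lies in what the count can be taken to mean.

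Second, a reader might infer that the planned test is generally pushed against the spa arm, or would show apparent harm. The documents do not support that. VII-3 records dates and days within the interval, so scoring an ongoing leave as one period is at least as natural as scoring only new ones. On that rule the spa arm does better at the lower relapse rates. Under neither rule does the expected difference reach 1.96 standard errors. Nor does the dependence on exposure vanish when the 1-year rates are equal, since earlier return alone changes the time at risk.

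Third, the weight is low. The item is absent from VI-2, the primary endpoint and days of leave are untouched, and a statistical analysis plan that is not shown may define the counting rule. But a counting rule would settle only the scoring. The count would still depend on time off the initial leave, and the decision to test it between arms is made in the protocol itself.

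Two other problems with the same variable are separate: there is no scheduled D0 value for the planned change from baseline, and the questionnaires are timed "from the enrolment visit for the control group and from the end of spa therapy for the intervention group". Repairing both would leave the present point in place.

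**Conclusion.** The point holds as a minor one. IX-1-6 tests between arms a count whose opportunity to accrue depends on the outcome the trial expects to change, and a low value does not separate sustained work from uninterrupted leave. The direction rests on two things the protocol does not give. With new periods only, the ratio is 1.14 near month 12 (about 1.17 to 1.18 over the simulated M6-M12 window) against the spa arm. With ongoing leave counted, the spa arm is better below about one relapse per returner per window, equal at one and worse above it.

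The ratio of 1.14 needs only the protocol's 70% and 80%, read as ended initial leave, and equal relapse per returner. The simulated figures also rest on exponential return and 14-day relapses. At these sizes the period comparison would more often than not be non-significant, beside a clear result on days of leave. The realistic consequence is a diluted or uninterpretable secondary result; apparent harm is not demonstrated.

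**What to change.** In IX-1-6, remove the number of periods of sick leave from the endpoints tested between arms. This also brings that item into line with VI-2. Keep days of leave between 6 months and 1 year as the tested sick-leave measure.

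Report periods by arm descriptively, as new periods that start after the end of the initial leave. Show beside them the days off leave in the window and the number of patients who never left the initial leave.

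The dates already collected under VII-3 suffice, so the cost is one sentence in the protocol and a short derivation. One between-arm test is lost. The rate per day off leave conditions on a post-randomisation event and should stay descriptive.

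### Section IX-1-6 puts sick-leave days and periods into a change-from-D0 mixed model that fits neither: periods have no D0 value, D0 days measure something else, and the follow-up windows differ in length

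*Protocol*

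**What the plan says.** Section IX-1-6 lists the outcomes for one linear mixed model as "number of days of sick leave, number of periods of sick leave, pain, Quebec scale, MOS SF-12, HAD, FABQ and CSQ". The response is a change: "The variable to be studied will therefore be the difference between the randomisation value (D0) and that of interest (1 year", and likewise for 3 and 6 months. The fixed effects include "the enrolment value as a quantitative covariate (centred variable), the visit variable (3 modalities". On correlation it says "A random effect on the patient will be added to this model". It also calls the model an MMRM, but states no variance by visit.

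Section VI-2 defines the secondary endpoint differently: "Number of days of sick leave between 6 months and 1 year after enrolment". It explains the restricted window: "We have not taken into account the total number of days of sick leave as, by definition, the intervention requires the patients". The reason it then gives is that attending the programme is itself a cause of leave.

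Section VII-3 sets what is collected at follow-up: "Periods of sick leave since the previous visit (dates and number of days of sick leave". In the assessment table of the General Outline, days of sick leave are ticked at D0, M3, M6 and M12. The row "Number of periods of sick leave" is ticked at M3, M6 and M12 only. Section VII-1 lists the start date of the current leave as the sick-leave item recorded at enrolment.

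**The concern.** A change-from-baseline model needs the same quantity measured on the same scale at baseline and at each visit. Pain and the questionnaire scores meet that condition; the two sick-leave variables do not. Taken at its word, IX-1-6 gives an analysis that cannot be run for periods. For days it gives a difference between two unlike quantities.

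The unequal windows raise a separate issue. A count over six months can reach about twice the maximum of a count over three, so its spread is likely to be larger. A model that assumes one spread for all visits then understates the uncertainty at M12, the visit that carries the endpoint. Sick-leave days form a stated secondary objective and are the secondary endpoint closest to return to work, so a false positive here would be read as support for the programme.

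**Working it through.** **Periods.** The model needs a D0 value twice, in the change and as covariate. The assessment table has none, and VII-1 collects only a start date. The analysis cannot be computed.

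**Days: what is subtracted.** Eligibility requires 4 to 24 weeks of leave, so elapsed leave at D0 lies between 4 × 7 = 28 and 24 × 7 = 168 days. The M12 value is a count within months 6 to 12, from 0 to about 182 days. A patient enrolled after 160 days who takes 20 days in months 6 to 12 has a change of −140; one enrolled after 30 days who takes the same 20 has −10. The endpoint is identical and the changes are not.

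**Does the subtraction distort the test?** No. With response Y − b and b also a covariate, Y − b = … + βb is the same model as Y = … + (β + 1)b. Only the coefficient of b moves. On one simulated data set, the change and raw-count models gave the same M12 group effect (−2.217) and standard error (4.258).

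**Unequal windows.** Inputs: two-sided 5% level (IX-1-5); three visits and a patient random effect (IX-1-6); windows of 3, 3 and 6 months (VII-3 with the visit schedule). Assumptions: complete data; one residual variance; the printed interaction between time and visit read as group by visit, because its stated purpose is a treatment effect at each visit; and an SD ratio r of M12 to M3/M6, since the protocol gives no SDs.

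In a balanced random-intercept fit, the variance used for every visit is the mean of the three visit variances, whatever the within-patient correlation. With SDs 1, 1, r:

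- assumed/true variance at M12 = [(2 + r²)/3] / r²
- true size at M12 = 2 × [1 − Φ(1.96 × √ratio)]

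| r | Variance ratio | SE as a share of the correct SE | Size at M12 | Size at M3 |
|---|---|---|---|---|
| 1.0 | 1.00 | 1.00 | 5.0% | 5.0% |
| 1.25 | 1.1875/1.5625 = 0.76 | 0.87 | 8.8% | 3.3% |
| 1.5 | 1.4167/2.25 = 0.63 | 0.79 | 12.0% | 2.0% |
| 2.0 | 2/4 = 0.50 | 0.71 | 16.6% | 0.6% |

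The first row reproduces the plan's nominal 5%.

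**Plausible SDs.** Two assumed return-to-work patterns were simulated with no treatment effect.

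- *Weibull return times, 70% back by 12 months (the control rate in IV-3), 15% relapse.* SDs are 34, 43 and 82 days. Pooled SD = √[(34² + 43² + 82²)/3] = 57; 57/82 = 0.69; size about 17%. Simulation at 300 per arm: 16.9%.
- *Faster return, about 15% still on the first leave at one year, with or without relapses.* SDs are about 32, 42 and 69 days. Pooled SD = √[(32² + 42² + 69²)/3] = 50; 50/69 = 0.73; size about 15%. Simulation at 300 and 350 per arm, 6,000 runs each: 15.1% to 15.8%.

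**One value per patient.** In the second pattern, months 6 to 12 days analysed alone gave a size of 4.9% to 5.6% by ANCOVA and 5.1% to 5.7% by Mann–Whitney, although 54% to 68% of values were zero.

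**The case against.** The strongest reply concerns the covariance. IX-1-6 says only that a patient effect is added, and it uses the label MMRM. A later analysis plan, which IX-1 promises, could allow a separate variance at each visit, and the M12 inflation would then largely go. This stands: the error-rate figure is conditional. It does not answer the points about D0, which no covariance structure repairs.

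A single-value analysis also loses something. The mixed model is justified partly by its use of incomplete follow-up when data are missing at random. That stands too, and the fix has to replace it.

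Four stronger readings are tempting but are not supported:

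- *The D0 mismatch inflates the error rate.* It does not, because D0 is also a covariate.
- *No D0 value exists for days.* One is ticked in the assessment table; it is simply not comparable.
- *The model contaminates the M12 estimate with the months that VI-2 leaves out.* With a group-by-visit term and complete data, the M12 contrast is the M12 group difference. Earlier windows enter through the variance and the handling of missing data.
- *The many zeros invalidate a linear analysis.* At 300 to 350 per arm they did little harm in the simulations.

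**Conclusion.** The point holds as a mismatch between the specified model and two of its outcomes. For periods, the analysis cannot be carried out; this variable is not among the endpoints in VI-2, so the consequence is limited. For days, a named secondary endpoint, the modelled change is not interpretable and does not correspond to the single-window count in VI-2.

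The error-rate part is a qualified addition. Under one residual variance, the size at M12 is about 9% to 17% against a nominal 5% for SD ratios of 1.25 to 2.0. These ratios are assumed. A reader might take 17% as the error rate of this trial, but the protocol supplies neither the SDs nor a settled covariance structure. The calculation also leaves out missing data, and any difference between arms in when the questionnaires are timed from (VII-1). The primary endpoint and its sample size are untouched.

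**What to change.** Remove both sick-leave variables from the change-from-D0 model in IX-1-6, and specify instead:

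- **Days.** One value per patient for months 6 to 12 after enrolment, derived from the recorded leave dates. Use ANCOVA with robust standard errors, adjusted for leave duration at D0, or the Mann–Whitney test that IX-1-6 already uses elsewhere. Report the difference in mean days with its 95% CI.
- **Missing M12 values.** Multiple imputation using D0, M3 and M6 sick-leave data, which restores the use of partial follow-up.
- **Periods.** A follow-up count with no D0 value.

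The cost is a change of wording in IX-1-6 and a little more analysis work for the imputation. No new data are needed.
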